#### Patient outcomes

##### Questionnaire

Patients in the triadic sub-study will be asked to answer a short questionnaire including the following dimensions:Quality of communication and decision-making for the patient and the next-of-kin when approaching the end of life (primary outcome for patients)Communication about preferences for information and involvement, health care personnel’ current compliance with these preferences, and trust in future complianceSatisfaction with information about the patient’s state of health, discharge, prognosis, and future health care needs, and with information and involvement concerning health care provided during and after admittanceSelf-efficacy in communicating with next-of-kin and health care professionals about future deterioration, about preferences for life-prolonging treatment in such a situation, and about health care when approaching the end of lifeProblem causing admittance being solved; satisfaction with arrival, stay, and discharge at the hospital; and trust in necessary health care in the futureConcrete preferences for information and who should participate in important decisions about health care, and assessment of the amount of information givenGeneral life satisfaction [48]Demographic information

##### Data from patient health records

The researchers will retrospectively go through the patients’ electronic health records, given sufficient project resources. We will collect documentation from 18 months before to 18 months after inclusion (or until death) on the following: ACP and other similar conversations, palliative care plans, life prolonging treatment and palliative care given, any decisions to limit such treatment or care, and the patients’ life stance or religious beliefs.

##### Data from national registries

The patient dataset will be coupled to individual data from national registries (from 18 months before to 18 months after inclusion (or until death). This allows description of the patient population and their use of health services, and to assess possible long-term effects of ACP. The registers include the Norwegian Registry for Primary Health Care, Norwegian Patient Registry, Norwegian Prescription Database and Norwegian Cause of Death Registry.

#### Next-of-kin outcomes

##### Questionnaire

Next of kin in the triadic sub-study will be asked to answer a questionnaire including the following dimensions:Quality of communication and decision-making for the patient and the next-of-kin when approaching the end of life (primary outcome for next of kin)Satisfaction with information about the patient’s state of health, discharge, prognosis, and future health care needs, and with information and involvement concerning health care provided during and after admittanceSatisfaction with information about the patient’s state of health, discharge, prognosis, and future health care needs, and with information and involvement concerning health care provided during and after admittance, and with the health care personnel’ understanding of the next-of-kin’s situationSelf-efficacy in communicating with the patient and health care professionals about future deterioration, about the patient’s preferences for life-prolonging treatment in such a situation, and about health care when the patient is approaching the end of lifeProblem causing admittance being solved, satisfaction with arrival, stay, and discharge at the hospital, trust in necessary health care for the patient in the future, and believe that you have to ensure that the patient receives needed health care in the time to comeNext of kin’s concrete preferences for information and assessment of the amount of information given, the patient’s preference for information and who should participate in important decisions about health careNext of kin’s tasks and burdensInformal carer’s care-related quality of life [60].General life satisfaction [48].Demographic information

#### Attending clinician outcomes

##### Questionnaire

Attending clinicians in the triadic sub-study will be asked to answer a questionnaire including the following dimensions:Clinical information about the patientThe professional role towards the patientThe patient’s concrete preferences for information and who should participate in important decisions about health care, and assessment of the amount of information given (primary outcome for attending clinicians is the congruence between the clinician’s answer and the patient’s answer on these questions)Self-confidence in matching involvement of patient and next-of-kin and future decision-making to patient’s preferencesSelf-efficacy in communicating about: future deterioration, preferences for life-prolonging treatment in such a situation, future care (at home or in a nursing home), and about health care when approaching the end of life, with the patient, next-of-kin, and other health care personnelDemographic information

#### Recruitment

A local research coordinator at each participating unit will recruit participants assisted by the health care personnel at the units, guided by a set of instructions and supervision by the researchers. All potential participants will be assessed for eligibility. The patients who fulfil the criteria will receive verbal and written information about the study from a health professional at the unit. If a written informed consent is obtained, the health professional will ask the patient for permission to contact the closest relative to inform and possibly obtain consent and include him or her, and subsequently inform and recruit the clinician. The patient, the next-of-kin and the clinician will be included if the whole triad consents to participate. At the time of submission of this manuscript, the units were just about to begin recruiting participants to the triadic sub-study.

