### Health care professionals and local unit leaders

Health care personnel will have many roles in the implementation, the ACP intervention, and the research in this study. According to the whole-ward approach, the project encourages the units to include all clinicians in the ACP training, and some will actively participate in the clinical intervention, by providing ACP as a part of the clinical care. Dedicated clinicians will be appointed to roles as ACP-coordinators and implementation teams, thereby performing tasks related to both implementation and research. The implementation teams consist of clinical staff with a special interest or expertise relevant to ACP, and the closest leader. In Norwegian hospitals, the local unit leaders are in general health care professionals using some or all their time to lead the unit or a part of the unit. A research coordinator will be responsible for recruiting patients and next of kin to the quantitative and qualitative studies in collaboration with the staff.

The study will collect data from the health care personnel in four sub-studies: The fidelity assessments, a quantitative study to all health care personnel and the unit leaders, and the triadic study including an attending clinician, in both the intervention and the control arms, and qualitative interviews with ordinary clinicians and with the implementation teams in the intervention units.

In the triadic sub-study, the participating clinician will also provide clinical data about the included patient. This participating clinician should be closely involved in the health care provided to the patient during the hospitalization and have sufficient knowledge of the patient’s health and health care needs. If feasible, the participating clinician will be the attending clinician responsible for the patient’s medical care. In the intervention arm, the participating clinician should also be the clinician who participated in the ACP.

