### Blinding

Due to the nature of the project, neither the units, the local leaders, the health care personnel nor the project’s researchers can be blinded to the hospital units’ allocation status. The project group is small, and the project’s researchers will contribute to all parts of the project, including developing the implementation program and providing the implementation support. This makes the researchers more familiar with and knowledgeable of all aspects of the units, which strengthens the tailoring of the intervention, and it improves the quality of the evaluation. On the other hand, having researchers evaluate the results of a program and the support they have provided themselves may lead to a risk of experimenter bias. This will be minimized by awareness of the risk of bias and by dividing the responsibility for the implementation and for the evaluation between different researchers. To prevent selection bias, patients and next of kin will not be informed about the hospital unit’s allocation status, but they may deduce this from the kind of treatment they receive. We assume that self-reported data and data collected from national registries to a low degree will be susceptible to bias.

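### A clinician's non-consent removes a consenting patient and relative from their own primary outcomes, under a stricter rule in the intervention arm, so selection after randomisation may differ by arm

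*Protocol article*

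**What the plan says.** Under Recruitment, the protocol article takes the patient's consent first, then the relative's, and only then does the unit "subsequently inform and recruit the clinician". Entry is all or nothing: "The patient, the next-of-kin and the clinician will be included if the whole triad consents to participate".

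The exclusion criteria for patients repeat this by arm. In the intervention arm, a patient is excluded when the clinician who took part in the ACP conversation has not consented to the research. In the control arm, the exclusion refers to an attending clinician. The section on health care professionals and local unit leaders says the same for the intervention arm: "In the intervention arm, the participating clinician should also be the clinician who participated in the ACP".

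The sub-study has three primary outcomes:
- The patient's own report on quality of communication and decision-making "when approaching the end of life (primary outcome for patients").
- The relative's own report on the same dimension "when approaching the end of life (primary outcome for next of kin").
- For the clinician: "primary outcome for attending clinicians is the congruence between the clinician’s answer and the patient’s answer on these questions".

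On blinding, the article states that "neither the units, the local leaders, the health care personnel nor the project’s researchers can be blinded". Its safeguard is: "To prevent selection bias, patients and next of kin will not be informed about the hospital unit’s allocation status".

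**The concern.** Two of the three primary outcomes are self-reports that can be analysed without any clinician answer. The rule nevertheless makes them depend on the consent of a third person who knows the arm and is approached after the other two have agreed. Units were randomised in August 2022 and triad inclusion starts about 13 months into the intervention, so this exclusion operates well after allocation. Randomisation of units does not balance it.

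The rule is also worded differently by arm. In the intervention arm it is tied to the clinician who took part in one particular conversation; in the control arm it is not. If willingness to consent is related to how communication went, and more so in one arm, the samples compared are no longer selected alike and the between-arm difference in these two outcomes is biased. Separately, people who agreed to give data are turned away for outcomes that their data alone would serve.

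**Working it through.** **1. Which primary outcome needs the clinician?**

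| Primary outcome | Source | Clinician answer needed? | Lost if clinician does not consent? |
|---|---|---|---|
| Communication and decision-making, patient | Patient questionnaire | No | Yes |
| Communication and decision-making, next of kin | Next-of-kin questionnaire | No | Yes |
| Congruence | Patient and clinician questionnaires | Yes | Yes, unavoidably |

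**2. Does another provision cover it?**
- The stated safeguard against selection bias concerns what patients and relatives are told. It does not touch the clinician's decision.
- Multiple imputation (Data analysis, triadic sub-study) handles missing data among participants. A triad that was never included has no record to impute.
- The comparison of included with all admitted patients uses basic anonymous clinical data from random periods. It cannot show how communication would have been rated in the triads that were lost.

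**3. The protocol's own sample size.** The inputs are 0.5 SD, ICC 0.05, six clusters per arm, 80% power and 5% (taken as two-sided).
- Without clustering: 63 per arm (normal approximation) or 64 (t-based).
- Design effect at 22 per cluster: 1 + 21 × 0.05 = 2.05, and 63 × 2.05 = 129.
- Solving for cluster size with 64: 64 × 0.95 / (6 − 64 × 0.05) = 60.8 / 2.8 = 21.7, rounded up to 22; 6 × 22 = 132.

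The stated 132 per arm is reproduced, and the sample size is not in dispute.

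**4. Size of the possible bias.** Let v be the share of otherwise eligible triads lost through clinician non-consent, and d the number of SDs by which those patients would have scored below the retained ones. The mean of everyone is then the retained mean minus v × d, so the retained mean is too high by v × d. The bias in the between-arm difference is

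bias = v₁d₁ − v₀d₀ (1 = intervention, 0 = control).

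The protocol gives neither v nor d. Assuming v₁ = 5–15%, d₁ = 0.5–1.0 SD and no selective loss in controls:

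| v₁ | d₁ = 0.5 | d₁ = 1.0 |
|---|---|---|
| 5% | 0.025 SD | 0.05 SD |
| 10% | 0.05 SD | 0.10 SD |
| 15% | 0.075 SD | 0.15 SD |

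Against the 0.5 SD target this is 0.025/0.5 = 5% to 0.15/0.5 = 30%. If v₀d₀ = v₁d₁, the bias is zero.

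**5. Effect on the test.** At 35 per cluster the design effect is 1 + 34 × 0.05 = 2.7, and SE = √(2 × 2.7 / 210) = 0.160 SD. With no true effect, a shift of 0.025 SD (0.156 SE) gives a two-sided 5% test a rejection rate of 5.3%; a shift of 0.15 SD (0.935 SE) gives 15.5% (normal approximation). With a t reference on 10 df the figures are 5.2% and 13.6%.

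**The case against.** The strongest reply is that the mechanism is inferred. Several stronger readings are tempting, and the document does not support them:

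- **That the clinician is being rated, or held the conversation.** The text says only that the clinician participated. The outcome covers communication and decision-making generally and is not described as a rating of that clinician.
- **That the clinician decides after the conversation, triad by triad.** The order patient, relative, clinician is stated. The timing relative to the conversation is not, although the past-tense criterion and the exclusion when ACP did not take place before discharge make it likely. The exclusion wording would also fit one standing consent, and the recruitment instructions are not shown.
- **That another clinician can step in for controls.** This is nowhere stated. In both arms the clinician should be closely involved with the patient and, if feasible, be the one responsible for the medical care. Control clinicians are equally unblinded and could also decline selectively.
- **That power is lost.** The target is at least 420 included triads (35 × 12). A declined triad costs recruitment effort but does not come out of the 35, so no power loss is claimed.

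The triad is also a deliberate choice: it lets three perspectives be compared, and the clinician supplies clinical data used to check that the arms are comparable.

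These points limit the size and certainty of the bias. They do not remove the rule itself. The comparison of perspectives justifies requiring the clinician for congruence, but not for two self-reported outcomes. The intervention-arm wording remains the stricter one.

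**Conclusion.** The point holds as a weakness of design. A consenting patient and relative are excluded from their own primary outcomes when an unblinded clinician, recruited last, does not consent. The criterion differs by arm and applies after randomisation, and the planned analysis cannot recover those triads.

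A reader might infer that the effect will be inflated. The document supports only that it could be. Overstatement requires that clinicians decline more often after poorer conversations, and that this selectivity is stronger in the intervention arm. The size is unknown: 0.025–0.15 SD is an illustration under assumed 5–15% loss, an assumed deficit of 0.5–1.0 SD and no selective loss in controls. With rare refusals it is negligible; with equal selectivity in both arms it cancels. The change is worth making because it is cheap and removes the mechanism whatever the true refusal rate.

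**What to change.** 1. Obtain each clinician's research consent once, before triad enrolment opens or when the clinician joins the unit, so that it cannot depend on a particular patient or conversation.
2. Keep every consenting patient and relative in the analyses of their own primary outcomes when the clinician does not consent. Require the clinician only for congruence.
3. Amend the two clinician-consent items in the exclusion criteria for patients, and the whole-triad sentence under Recruitment, to match.
4. Report by arm the number of otherwise eligible triads in which the clinician did not consent.

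The article says units were just about to start recruiting at submission. If triads have been enrolled under the present rule, record the date of the change and report refusals before it as well, where they are known.

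Cost: a change of consent procedure and criteria wording. Denominators will differ slightly across the three primary outcomes. Clinician-supplied clinical data will be missing for the added patients, which slightly weakens the check that the arms are comparable.

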#### Data analysis

Demographic and clinical data about the patients will be used to assess whether the patients in the control and intervention units are comparable. In addition, the participating units will collect basic and anonymous clinical information about all patients admitted to the units at shorter random time periods, to get more information about the participant units and to compare the included patients with all admitted patients.

Number and percentages of invitation to and participation in ACP for patients and next of kin will be calculated and compared between intervention and control group. The primary statistical analyses will be the difference in mean outcomes between participants in the intervention and the control group using linear mixed effects models. The random part of the model will consist of random intercept for patient or relative identification nested within centre. Missing data will be handled by multiple imputation using predictive means matching with 100 imputed data sets.

If the analyses show differences in the intervention and control arm, we will perform analyses to assess if higher fidelity score (higher levels of implementation) is associated with improved outcomes for patients, next of kin, and clinicians. For the secondary outcomes, we will compute average outcomes and SD for the intervention and the control group and use the t-test to determine if there is a significant difference between groups.

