### Secondary objectives

To measure the present level of implementation of ACP in all participating hospital units.To evaluate whether the implementation support, relative to no support, is associated with improved implementation of ACP, measured with the ACP fidelity scale (sum score, the quality subscale, the implementation subscale and the penetration rate subscale).To identify barriers to, facilitators for and experiences with implementing ACP among the stakeholders at the a) clinical, b) health care service- and c) municipal, regional and national level.To explore moral dilemmas and conflicting interests related to ACP, and strategies on how to resolve them.To explore benefits and disadvantages with ACP among patients and their next of kin, and to explore the benefits and disadvantages of both the implementation support and ACP among health care personnel and the implementation teams.To investigate whether the implementation support is associated with improved quality of communication and decision-making when approaching the end of life for patients and next of kin, better congruence between the patient’s preferences for information and involvement and the attending clinician’s perceptions of the same, and improvements of other relevant outcomes for patients, next of kin and the attending clinician.To assess whether higher level of implementation (fidelity) of ACP is associated with improved outcomes for patients, next of kin, the staff and the services.To measure, before and during the implementation process, health care personnel’s perceptions, attitudes, self-efficacy, confidence in, and experiences in relation to information giving and involvement of patients and next of kin.To measure healthcare utilization, costs, and the cost-effectiveness of the implementation and of ACP in the routine health care in hospital units.

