The units were sorted from one to 12 according to the number of geriatric beds and then stratified into three strata: four clusters with 16 to 23 beds, six clusters with 6 to 10 beds and two clusters with 4 and 5 beds respectively. In each block, the clusters were randomized to either the intervention or the control arm with an allocation ratio of 1:1. An independent professor in epidemiology performed the allocation using the Microsoft Excel RAND-function, only knowing the numbers of the clusters. The randomization was performed to achieve a balance in unit types in the intervention and control arm and a similar size of the two arms including a similar number of admitted patients filling the inclusion criteria. All hospitals are located in cities or towns. The purpose of the stratification was primarily to achieve a balance in the number of patients and next of kin between the two arms, and secondly to include units of various sizes in both.

The study has primary outcomes for the implementation and for the clinical effectiveness. The primary outcome for the implementation outcome sub-study is the differences in fidelity changes between the arms. The unit of analysis for the fidelity scores is the health care units or clusters. Fidelity is rated on 5-point scales (1 = poor fidelity, 5 = high fidelity). Based on previous research (mean difference 1.82 and average SD 0.80 after 18 months with implementation support), we have calculated that we need at least four clusters in each arm to show that implementation support gives a significant increase in fidelity, based on 5% two-tailed significance and 80% power. If the differences are smaller in our study, we will need a larger sample. Due to the possibility of unit drop-out during the project period and to secure sufficient power, we have included six units in the intervention arm and six in the control arm.

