#### Data collection

We defined baseline as the situation before the start of the intervention, and the baseline fidelity measurements were conducted from May to August 2022. The participating hospital units were randomized to the intervention- or control arm after the baseline fidelity measurement in August 2022. The implementation period started with kick-off on Oct 25th, 2022, and will continue for approximately 18 months (when the inclusion for the triadic sub-study is completed, and before the last measurement of fidelity). Fidelity measurements in the intervention arm will be at baseline, at 7–10 months after the start of the intervention (May to August 2023) and at 18 months (April 2024). Fidelity measurements in the control arm will be at baseline and at 18 months. The second fidelity measurement is not done in the control group due to resource considerations, and to avoid influencing clinical activity in the control arm.

The fidelity scores at each unit will be based on a) interviews with leaders, b) interviews with resource persons, c) interviews with physicians, d) interviews with nurses, e) written material (e.g., information brochures or clinical procedures) and f) existing routine data (number of patients eligible for/offered/received ACP). Seven of the project members participate in the data collection, forming teams of two people visiting each site. Based on the interviews and available information, the two researchers will, at the end of the visit, score fidelity individually, and subsequently discuss possible discrepancies and decide on a consensus score.

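### The fidelity–outcome analysis is run only if the arms differ, although it is an unconditional secondary objective, and no arm term is named to separate fidelity from allocation

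*Protocol article*

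**What the plan says.** The Secondary objectives of the protocol article include, with no condition attached: "To assess whether higher level of implementation (fidelity) of ACP is associated with improved outcomes for patients, next of kin, the staff and the services".

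The Data analysis section of the triadic sub-study attaches one: "If the analyses show differences in the intervention and control arm, we will perform analyses to assess if higher fidelity score" is associated with better outcomes for patients, relatives and clinicians. It does not say which comparison or outcome has to differ, or what model will be used. It mentions no arm term, within-arm contrast or mediation approach, and neither does the rest of the article.

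Three other statements bear on the point:
- Fidelity is scored once per unit: "The unit of analysis for the fidelity scores is the health care units or clusters". With "we have included six units in the intervention arm and six in the control arm", that gives 12 values.
- Both arms are scored: "Fidelity measurements in the control arm will be at baseline and at 18 months".
- The arms are planned to differ widely in fidelity. The sample-size section uses "mean difference 1.82 and average SD 0.80 after 18 months with implementation support".

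**The concern.** There are two linked problems.

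**The condition contradicts the objective.** If the plan is followed as written, a null arm comparison leaves a listed objective unaddressed. The Discussion itself warns that outcome differences between arms may not be large, so this is not a remote case.

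**Fidelity is tied to allocation.** Raising fidelity in one arm is the primary implementation hypothesis. Once the arms are known to differ in outcome, asking whether higher-fidelity units did better largely repeats the arm comparison, unless the model separates fidelity from arm. At stake is a reported conclusion that better implementation improves outcomes, with no evidence for it beyond the arm effect. The primary comparisons are not affected.

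**Working it through.** **Inputs.** From the sample-size section: fidelity difference 1.82, SD 0.80; clinical effect 0.5 SD; ICC 0.05; six units per arm; 22 patients per unit required and 35 targeted. Assumptions: 0.80 is the within-arm SD of the fidelity score used, unit sizes are equal, and the arms differ when a two-sided 5% t-test on unit means (10 df) favours the intervention.

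**Reproducing the plan's figures.**
- Fidelity ("based on 5% two-tailed significance and 80% power"): n per arm = 2 × [0.80 × (1.96 + 0.84) / 1.82]² = 3.03, rounded up to 4, as stated.
- Clinical: 0.5 SD needs 63 per arm (normal) or 64 (t-based). The design effect is 1 + 21 × 0.05 = 2.05. Then 64 × 2.05 = 131.2, or 21.9 per unit, which rounds to the stated 22 and 132.

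**How often the condition fails.** At 35 per unit the SD of a unit mean is √(0.05 + 0.95/35) = 0.278. The SE of the arm difference is 0.278 × √(2/6) = 0.160, so the standardised effect is 0.5/0.160 = 3.1. Power on 10 df is 80.1%, so the analysis is not run in about 20% of trials with a true 0.5 SD effect.

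**How closely fidelity follows arm.** The between-arm variance is 1.82²/4 = 0.828 and the within-arm variance is 0.80² = 0.640. The large-sample correlation is √(0.828/1.468) = 0.75; the simulated average with 12 units is 0.77.

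**What a slope without arm would show.** Simulation, 200,000 trials per scenario: fidelity differs by arm but has no relation to outcome within either arm. Unit means are regressed on fidelity, without and with arm. The columns without arm count significantly positive slopes only (nominal 2.5%); the last column is two-sided (nominal 5%).

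| Scenario | Condition met | Without arm, all trials | Without arm, condition met | With arm, condition met |
|---|---|---|---|---|
| Plan inputs, 35 per unit | 80.1% | 45.5% | 53.6% | 4.9% |
| 22 per unit | 72.6% | 40.4% | 51.2% | 5.1% |
| Arm effect 0.3 SD | 39.5% | 22.4% | 44.0% | 4.9% |
| Fidelity difference 2.5 | 80.3% | 58.6% | 69.5% | 5.0% |
| Fidelity difference 1.0 | 80.4% | 22.2% | 25.3% | 5.0% |
| Fidelity difference 0.5 | 80.2% | 9.3% | 10.2% | 4.9% |
| No arm effect | 2.5% | 2.5% | 36.8% | 5.5% |

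At the plan's inputs, among trials meeting the condition, the slope without arm is positive in 99.7% and averages 0.185 SD per fidelity point. With arm in the model it averages 0.00.

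**What the arm-adjusted analysis can detect.** Suppose the whole effect runs through fidelity, within arms as well as between them: slope 0.5/1.82 = 0.275 per point. The arm-adjusted test then has 57.6% power over all trials and 52.6% among those meeting the condition. In this scenario the arm test itself succeeds in only 59.7% of trials, because within-arm fidelity adds about 0.275² × 0.64 = 0.048 to the between-unit variance. The condition would then block the analysis in about 40% of trials in which fidelity truly matters.

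**The case against.** **No model is stated.** The Data analysis section names neither a pooled slope nor the omission of arm. The covariates of a secondary analysis are commonly left to an analysis plan, and one that included arm would remove the false association. This stands. A reader might infer that the plan specifies an unadjusted slope and will therefore confirm a dose–response; the text does not say so.

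**The condition alone does not create the bias.** With arm in the model, the rate among trials meeting the condition is 4.9%. Without arm, at the plan's inputs, the condition raises the rate only from 45.5% to 53.6%. So a reader should not infer that the condition makes the conclusion automatic, or that deleting it is enough. This also stands.

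**Fidelity is not simply arm under another name.** A correlation of 0.77 leaves about 40% of the fidelity variance within arms (1 − 0.77² = 0.41). A within-arm SD of 0.4 to 0.5 would put the rate at 66% before any conditioning, but the document gives 0.80.

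**The objective asks only about association.** If allocation raises both fidelity and outcome, a marginal association is genuine, and it misleads only if read as independent of arm. That is fair, and it is a reason to label an unadjusted result clearly. The within-arm slope has its own weakness, since it sets aside the randomised variation in fidelity.

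None of this removes the conflict between an unconditional objective and an explicit condition. That is stated text and not silence.

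**Conclusion.** The point holds in two parts of different strength. The firm part is the contradiction: the objective is unconditional but its analysis is conditional, so it goes unaddressed in about 20% of trials with a true 0.5 SD effect at 35 per unit (about 27% at 22 per unit).

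The second part is a risk that depends on a model the article does not state. If arm were left out, a significantly positive slope would appear in about 45% of trials, and in 53 to 54% of those meeting the condition, with no within-arm relation. The latter figure falls to 25% and 10% at fidelity differences of 1.0 and 0.5. With arm included it is about 5% throughout.

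These figures rest on 0.80 as the within-arm SD of fidelity, equal unit sizes, and a significant result in favour of the intervention as the condition. The change should be made, but it concerns a secondary analysis only.

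**What to change.** In the triadic sub-study's Data analysis section:

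1. Delete the condition on the arm comparison, so that the analysis is always done and matches the Secondary objectives.
2. Fit each outcome on the unit-level fidelity score with arm as a fixed effect and a unit random intercept. Fidelity and arm are both unit-level, so about 12 − 3 = 9 degrees of freedom are available for the slope.
3. Report the within-arm slope with its confidence interval, labelled exploratory and non-randomised.
4. If an unadjusted association is also shown, state that it cannot be separated from the arm effect.

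The cost is analysis wording only; no data collection changes. The drawback is imprecision: with 12 units, power for the within-arm slope is about 53 to 58% even if the whole effect runs through fidelity. A null slope should therefore not be read as showing that fidelity does not matter.
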